### Outcomes

The primary outcome measure of this trial is the change of weekly urticaria activity score (UAS7) at week 12. There are multiple secondary outcomes, including the change of UAS7 score at week 6 and 16, the change of Urticaria Control Test (UCT), Visual Analog Scale of Itch Severity (VAS), Chronic Urticaria Quality of Life Questionnaire (CU-Q2oL) and Angioedema Activity Score (AAS), at week 6, 12 and 16, the change of immunoglobulin E (IgE) test and gut microbiota test at week 12, and the use of the standard antihistamine therapy (Bilastine) during the entire study period.

### Intervention

In this trial, the dose of standard therapy of antihistamine, Bilastine, is 20 mg once daily during the first 6 weeks of treatment, and on-demand basis during 6th-12th weeks. Participants will be allowed to increase dose of Bilastine up to 20 mg stat dose in case of insufficient control of symptoms according to EAACI/GA2LEN/EDF/WAO 2017 guidelines [3]. The dose of the investigational Chinese medicine formula granules, mXFP, is 19.4 g each time, twice daily in the treatment group while the placebo granules is 19.4 g each time, twice daily in the control group. All participants will be randomly assigned at a 1:1 ratio into two groups to receive the granules.

Moisturiser is not prohibited for use during the study. However, any additional treatment other than the standard western therapy and Chinese medicine granules after randomization is prohibited. Besides, participants will not be allowed to take prebiotics and probiotics during the study.

### Safety

No documented severe or serious event was reported using this herbal formula [23, 24]. However, there are still minor adverse events such as abdominal pain and dyspepsia. [25]. Safety will be assessed by laboratory parameters and participants’ reported adverse events and/or serious adverse events. All participants will be suggested to inform the study team about any adverse reaction during the treatment and follow-up periods. A direct telephone line will be provided so that subjects can report any adverse events during office hours between scheduled visits. Participants will be arranged to see our doctors if needed as unscheduled visits. All adverse reaction will be recorded, and the treatment suspended when any severe adverse reaction occurs.

Besides, in order to ensure participants’ safety, general data and routine blood test will be done before taking the medications. Blood test may induce bleeding, infection, bruising, and feeling lightheaded. When the needle pricks participant’s arm or hand, the participant may suffer a mild painful feeling, and the site maybe sore afterward. However, the risk of blood test is very low and discomfort is mild.

### Recruitment

CU participants will be recruited from the following Chinese medicine clinics: (1) The CUHK Chinese Medicine Specialty Clinic and Teaching and Research Centre on CUHK campus (CUHK-CMSCTRC); (2) The two Integrative Medical Centres, Hong Kong Institute of Integrative Medicine at Sha Tin and Wan Chai. Advertisements in the poster on the clinic and internet platforms, such as Facebook, emails, and website will be made to facilitate community recruitment. Besides, we will publish articles in local newspapers and magazines as well as organize health promotion talks to augment the patient recruitment process. Potential participants with CU who meet the eligibility criteria will be recruited.

### Randomisation and blinding

A random number table will be generated with a computerized random number generator program. The random allocations will be put into opaque envelops with sequential study numbers. Two sets of the envelope will be prepared, with one set for randomization at the site and another set stored in the investigator’s office for emergency unblinding. Each participant will be assigned with a sequential study number and then the corresponding allocated herbal granules or placebo will be prepared according to the random allocation sequence by an independent research staff member. The dosages will be prepared according to CMP’s instruction. During the study, the CMP investigators, study participants and outcome assessors will be kept blind of the allocated intervention.

### Trial procedures and follow-up

As shown in the Fig. 1 and Table 1, each partcipant has a phone call or face-to-face interview in screening and a total four visits to the Chinese medicine clinic throughout the study. Community participants who express interest in our study and agree for our telephone screening will leave their contact to project research assistant while potential participants referred from the wards, clinics or medical centres will be screened directly. Eligible subjects after screening will be arranged for a face-to-face or telephone interview for eligibility assessment. UAS7 will be delivered and filled by participants 7 days before the baseline visit.

**Fig. 1 Fig1:**
[figure not shown]
Study flow chart

**Table 1 Tab1:** SPIRIT schedule of enrolment, interventions, and assessments

	Study period				
	Screening	Treatment period			Post treatment follow up
Timepoint	−7 to 0 days	Day 0 (baseline)	Week 6 (±4 days)	Week 12 (±4 days)	Week 16 (±4 days)
Enrolment					
Informed consent	X				
Eligibility screen	X	X			
Medical consultation and assessment	X	X	X	X	X
Medical history	X				
Concomitant medication	X	X	X	X	X
Intervention					
mXFP/ Placebo and Bilastine		X	X		
Outcome Assessment					
Weekly urticaria activity score (UAS7)	X	X	X	X	X
Urticaria Control Test (UCT)		X	X	X	X
Visual Analog Scale of Itch Severity (VAS)		X	X	X	X
Chronic Urticaria Quality of Life Questionnaire (CU-Q2oL)		X	X	X	X
Angioedema Activity Score (AAS)		X	X	X	X
Serum levels of IgE	X			X	
Gut microbiota		X		X	
AE/SAE assessment			X	X	X
Laboratory Assessment					
CBP with differentiation	X			X	
Renal and Liver function test	X			X	
Thyroid function test (FT3, FT4 and TSH)	X				

For the baseline visit, eligibility will be checked and information about the study will be explained to the participants who will sign informed consent form voluntarily at their agreement afterward. Participants will be taken for not more than 20 ml of blood for complete blood count (CBC), liver function test (LFT), renal function test (RFT), and thyroid function test (FT3, FT4 and TSH) as safety measures while total immunoglobin E (IgE) as one of the outcomes for the measurement of inflammation. Then participants will be randomly assigned at a 1:1 ratio to receive 6 weeks of either mXFP granules 19.4 g each time or placebo granules 19.4 g each time twice daily. All participants will take the standard therapy of Bilastine 20 mg once daily during the first 6 weeks of treatment, and on-demand basis for the subsequent 6 weeks. They will be allowed to increase the dose of oral Bilastine up to 20 mg stat dose in case of insufficient control of symptoms according to EAACI/GA2LEN/EDF/WAO 2017 guidelines [3]. Baseline demographic data, medical history and drugs including use of moisturiser will be taken. UAS7, UCT, VAS, CU-Q2oL, and AAS will be completed. Participants will start study treatment after stool collection and notification of non-clinically significant blood results for the safety measures. Relevant information on the use and storage of study drugs will be recorded.

Participants will return for follow-up at week 6 (± 4 days), week 12 (± 4 days), and be followed by a post-treatment visit at week 16 (± 4 days). UAS7, UCT, VAS, CU-Q2oL, and AAS will be collected at every follow-up visits. At the 3rd follow-up visit at week 12, stool samples and blood samples for CBC, LFT, RFT and total IgE will be collected. Adverse events will be recorded for safety monitoring.

Throughout the study, participants are required to keep a daily record for their compliance and side effects of the study treatment, if any. Also, the participants are advised to record all the other medication, including health food supplements during the period of study. For the stool sample, as the food intake may affect the gut species and influence the gut microbiome analysis result, participants are required to record three days’ food diary before the day of taking faecal specimen.

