### Exclusion criteria

Subjects are excluded if they meet the any one of the following criteria:Dual deficiency of Qi and blood according to Chinese medicine theoryUrticaria is induced by physical factors (e.g., cold urticaria, delayed pressure urticaria, solar urticaria, heat urticaria, vibratory angioedema) only;Known to have dermatological diseases with skin pruritus;Known to have any serious diseases such as cancer, severe kidney and liver impairments, autoimmune disease, thyroid disease, Hodgkin’s disease, lymphoma, severe mental disorders, leukemia, and acute infectious disease;Known to use oral/injectable corticosteroids, leukotriene inhibitors, immunosuppressants or other Chinese herbal medicine within one month of enrollment;Known to receive omalizumab, ligelizumab, or other experimental biologic for CU;Documented pregnancy or planning to conceive, breast-feeding women; orOperate heavy machinery or need to drive motor vehicles as an essential part of their profession.Known to recent history (within previous 12 months) of drug addiction or alcohol abuse.Involved in other interventional clinical studies at the same time.Use antibiotics, prebiotics and probiotics within 4 weeks before study treatment commencement.

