### Sample size

The primary outcome is the UAS7 after 12 weeks of treatment. The minimal clinically important difference of UAS7 for measuring chronic urticaria ranges from 9.5 to 10.5 [26–28]. The standard deviation was estimated to be 12 from a previous study about the treatment of Chinese herbal formulae including Xiao-Feng Powder on Chinese patients with CU [24]. To detect a clinically meaningful difference of 10 in UAS7, with 80% power at the 0.05 significance level and an expected standard deviation of 12, 24 cases in each group are needed. To account for potential dropouts, a total of 58 subjects will be needed. PASS 12.0 was used for the sample size calculation.

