### Statistical analysis plan

All analyses will be conducted according to the intention-to-treat principle. Descriptive statistics will be computed for each of the analysed variables. The primary efficacy analysis will be done by comparing the two groups with respect to the UAS7 at baseline and at 6, 12 and 16 weeks after randomization using analysis of covariance (ANCOVA). Supplementary analyses will include a complete-case analysis and a linear mixed model analysis of all available data. Repeated measures ANCOVA will be used to test for group differences in the secondary outcomes, with adjustment for relevant baseline covariates. All statistical tests will be two-sided, and *p* < 0.05 is considered significant difference. The statistical software of SPSS 23.0 will be used for analysis.

Adverse events will be categorized, and the percentage of those experiencing mild and serious adverse events will be documented. Chi-square tests will be performed to examine differences in the proportion of total and categories of adverse events within each group.

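### The baseline-visit text randomises before the safety blood results that gate dosing are known, and takes consent after the entry UAS7 diary, whereas Table 1 gives a different order

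*Protocol article*

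**What the plan says.** All references are to the protocol article.

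- **Trial procedures and follow-up, before Table 1:** "UAS7 will be delivered and filled by participants 7 days before the baseline visit". Inclusion criteria make a UAS7 above 10 a condition of entry.
- **Same section, baseline-visit paragraph after Table 1:** eligibility is checked and the study explained to participants "who will sign informed consent form voluntarily at their agreement afterward". Blood is drawn for blood count, liver, renal and thyroid function and IgE. The text continues "Then participants will be randomly assigned at a 1:1 ratio to receive 6 weeks of either mXFP granules", and towards the end of the paragraph "Participants will start study treatment after stool collection and notification of non-clinically significant blood results for the safety measures".
- **Table 1:** consent is ticked at Screening only (−7 to 0 days). Blood count, renal and liver function, thyroid function and IgE are ticked at Screening and not at Day 0 (all but thyroid are repeated at week 12). The intervention is ticked from Day 0.
- **Exclusion criteria:** the list of known serious diseases includes "severe kidney and liver impairments, autoimmune disease, thyroid disease".
- **Ethical consideration and dissemination of information:** consent forms are to be signed before the study.
- **Sample size:** the primary outcome is UAS7 once 12 weeks of treatment have been given. The target difference is 10 points. The calculation reads "with 80% power at the 0.05 significance level and an expected standard deviation of 12, 24 cases in each group are needed", and the total is raised to 58 for dropouts.
- **Statistical analysis plan:** intention to treat applies to all analyses, and UAS7 is compared at 6, 12 and 16 weeks counted from randomisation.

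**The concern.** The text and the table cannot both be followed. If sites follow the text, allocation comes before the results on which dosing depends. Someone can then be randomised and not start treatment because of their bloods. The article does not say how such a person is handled, but its intention-to-treat rule keeps them in the comparison, where they pull the observed difference towards zero. In a trial of 58, a few such people matter.

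Two further consequences follow. The diary used for entry would be completed before consent, which conflicts with Table 1 and with the ethics section. And the 12-week clock would start at randomisation while treatment starts later, so the two descriptions of the primary time point no longer coincide.

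**Working it through.** **1. Order of events**

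| Step | Text | Table 1 |
|---|---|---|
| UAS7 diary for entry | 7 days before the baseline visit | Screening and Day 0 |
| Consent | Baseline visit, so after the diary | Screening |
| Safety bloods and IgE | Baseline visit | Screening |
| Randomisation | Baseline visit, after the blood draw | No row |
| Start of treatment | After stool collection and notified results | Day 0 |

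The Screening column includes day 0, so drawing blood on the day of the baseline visit is not ruled out by the table. That would still not place consent ahead of a seven-day diary finished before that visit.

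**2. Reproducing the planned size**

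Inputs: difference 10, SD 12, alpha 0.05, power 80% (Sample size); "All statistical tests will be two-sided" (Statistical analysis plan).

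- Normal approximation: n = 2 × (1.960 + 0.842)² × 12² / 10² = 22.6, so 23 per group.
- Two-sample t-test (noncentral t): n = 23.6, so 24 per group, with power 80.7%.

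The stated 24 is reproduced. The total of 58 is 29 per group, which leaves 58 − 48 = 10 places for dropout (10/58 = 17%). The article states no dropout rate.

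**3. Dilution from non-starters**

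Let f be the share of analysed participants who never start. Bloods are taken before dosing and allocation is random, so f is expected to be equal in the two arms. Non-starters receive neither mXFP nor placebo and contribute no difference:

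observed difference = (1 − f) × 10 + f × 0 = 10 × (1 − f).

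Two-sided t-test power with the SD held at 12:

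| f (assumed) | Difference | 24 per group | 29 per group |
|---|---|---|---|
| 0% | 10.0 | 80.7% | 87.7% |
| 2% | 9.8 | 79.1% | 86.3% |
| 5% | 9.5 | 76.6% | 84.2% |
| 10% | 9.0 | 72.0% | 80.1% |

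The 24-per-group column is the planned situation, in which the dropout allowance has been used by other losses. The 29-per-group column assumes that nobody is lost. At f = 10%, 58 × 0.10 = 5.8, so about 6 people are affected.

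**4. Treatment received by week 12**

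With the visit at 12 × 7 = 84 days from randomisation and a result delay of d days, treatment received is 84 − d days. For d = 0 this is 84 days (12 weeks). For d = 7 (assumed) it is 77 days (11 weeks).

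**The case against.** The order in the text rests largely on one word, *Then*, in a paragraph that is not strictly chronological: after randomisation it describes Bilastine use to week 12 and only afterwards returns to baseline demographics and questionnaires. The flow chart that might settle the order is not available here. Table 1 and the ethics section both point to early consent, so the consent sentence may be loose drafting. These points lower confidence about what sites will actually do. They do not remove the contradiction, because randomisation before results remains the plain reading and Table 1 says otherwise.

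Several stronger readings are tempting, and the article does not support them.

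- *The bloods decide eligibility.* The text calls them safety measures, and the kidney, liver and thyroid exclusions concern known disease. That an abnormal result makes someone ineligible is an inference.
- *Post-randomisation exclusions are built in.* Nothing in the article excludes a randomised participant, and intention to treat would retain them.
- *Non-starters use up the 10 spare places and also dilute the effect.* The same person cannot do both. If retained with outcome data, they take no dropout place.
- *Treatment at week 12 is shortened by the visit window as well.* The ±4 days apply under any order of events, so only the result delay can be charged to this point.
- *The comparison is biased between arms.* Both blinded arms wait for results in the same way. The expected effect is attenuation and shorter exposure.

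**Conclusion.** The contradiction between the baseline-visit text and Table 1 is real and should be resolved. It covers the order of consent, diary, bloods, allocation and first dose. Sample size and Statistical analysis plan also use different time origins, which agree only if dosing starts at randomisation.

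The direction of the effect under the text is clear, but its size is not known, because the article gives neither the share of non-starters nor the laboratory delay. The ranges of 0–10% and 0–7 days are assumptions, and both include zero. Within them, power at the planned 24 evaluable per group falls by up to 80.7 − 72.0 = 8.7 percentage points. With all 29 analysed it stays at or just above the 80% target. The figures also assume an unchanged SD and equal non-starter shares in the two arms. This is an avoidable loss of precision and clarity that can be corrected cheaply, and it does not undermine the validity of the randomised comparison.

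**What to change.** Reconcile the baseline-visit text with Table 1 on four points:

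1. Place consent before the UAS7 diary used for entry.
2. Open the randomisation envelope only after the blood results have been reviewed and the stool sample is in.
3. Use one time origin in Table 1, Sample size and Statistical analysis plan. Randomisation is the natural choice once dosing follows it directly.
4. Reconcile the visit count. The article allows telephone screening and gives four clinic visits (baseline, weeks 6, 12 and 16), which leaves telephone-screened participants no attendance before baseline for Table 1's consent and bloods.

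The planned 24 per group and 58 in total do not change. If bloods stay at the baseline visit, the cost is a few days between that visit and allocation. This adds no wait before dosing, since participants already wait for results. If Table 1 is followed, the cost is one extra attendance for telephone-screened participants.

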### Sample size

The primary outcome is the UAS7 after 12 weeks of treatment. The minimal clinically important difference of UAS7 for measuring chronic urticaria ranges from 9.5 to 10.5 [26–28]. The standard deviation was estimated to be 12 from a previous study about the treatment of Chinese herbal formulae including Xiao-Feng Powder on Chinese patients with CU [24]. To detect a clinically meaningful difference of 10 in UAS7, with 80% power at the 0.05 significance level and an expected standard deviation of 12, 24 cases in each group are needed. To account for potential dropouts, a total of 58 subjects will be needed. PASS 12.0 was used for the sample size calculation.

### Statistical analysis plan

All analyses will be conducted according to the intention-to-treat principle. Descriptive statistics will be computed for each of the analysed variables. The primary efficacy analysis will be done by comparing the two groups with respect to the UAS7 at baseline and at 6, 12 and 16 weeks after randomization using analysis of covariance (ANCOVA). Supplementary analyses will include a complete-case analysis and a linear mixed model analysis of all available data. Repeated measures ANCOVA will be used to test for group differences in the secondary outcomes, with adjustment for relevant baseline covariates. All statistical tests will be two-sided, and *p* < 0.05 is considered significant difference. The statistical software of SPSS 23.0 will be used for analysis.

Adverse events will be categorized, and the percentage of those experiencing mild and serious adverse events will be documented. Chi-square tests will be performed to examine differences in the proportion of total and categories of adverse events within each group.

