### Ethical consideration and dissemination of information

This study will be conducted according to the Declaration of Helsinki and ICH-GCP. The ethical validity of the study was approved by the Joint The Chinese University of Hong Kong–New Territories East Cluster Clinical Research Ethics Review Committee (CREC Ref. No. 2021.085 T). Any modifications to the protocol will be reported to this committee, and amendment approval should be obtained before any changes can take place. Participants will be informed that the confidentiality of all information and data will be maintained anonymity. Consent forms should be signed by the participants before the study. All information will be encrypted and only the involved investigators can have access. Password is required to access the data. Participants are free to withdraw at any time without giving a reason or punishment.

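### Intention-to-treat is fixed for all analyses, so the adverse event percentages keep randomised participants who never took granules in the denominator

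*Protocol article*

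**What the plan says.** The Statistical analysis plan section begins: "All analyses will be conducted according to the intention-to-treat principle". The rule carries no qualifier. After the efficacy methods, the same section turns to harms: "Adverse events will be categorized, and the percentage of those experiencing mild and serious adverse events will be documented". It then adds: "Chi-square tests will be performed to examine differences in the proportion of total and categories of adverse events within each group". No denominator is given for these percentages, and nothing elsewhere in the article limits the intention-to-treat rule to efficacy.

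Two places bear on whether a randomised participant might never be dosed. In Trial procedures and follow-up, the baseline visit text has the blood draw first, then "Then participants will be randomly assigned at a 1:1 ratio to receive 6 weeks of either mXFP granules", and later in the same paragraph "Participants will start study treatment after stool collection and notification of non-clinically significant blood results for the safety measures". Table 1, by contrast, puts the blood count, the renal, liver and thyroid function tests and IgE in the screening column (−7 to 0 days). The Ethical consideration section adds: "Participants are free to withdraw at any time without giving a reason or punishment".

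**The concern.** Intention-to-treat protects an efficacy comparison, because keeping everyone as randomised preserves the balance of the arms and tends to understate benefit. For harms, understating is the wrong direction. A participant who never took the product cannot react to it, yet counts as one of those observed to be free of a reaction. Each such person lowers the reported rate and, if the arms are similarly affected, shrinks any true excess on mXFP.

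The Objectives section names safety alongside efficacy. With 58 participants in total, a single person per arm is a visible share of the denominator. If the rule stands, the published safety percentages would look slightly better than the experience of those who took the granules.

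**Working it through.** **Inputs**
- Difference 10, standard deviation 12, two-sided 0.05, power 80%, 24 per group, 58 in total (Sample size; sidedness from Statistical analysis plan).
- Allocation 1:1 (Intervention), so 58/2 = 29 per arm.
- Number randomised but never dosed, *k* per arm: not in the article. Assumed to be 1 to 3, with 5 as an extreme bound.
- Adverse event rates among the dosed: not in the article. Assumed, for illustration only, to be 30% on mXFP and 10% on placebo, an excess of 20 points.

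**Step 1. The plan's own figures.** A two-sample t test with difference 10 and standard deviation 12 has power 0.789 at 23 per group and 0.807 at 24, so the stated 24 reproduces. The total of 58 leaves 58 − 48 = 10 for dropout, that is 10/58 = 17.2%, or 29 − 24 = 5 per arm. This covers loss over the whole study. Treating all of it as never dosed is therefore an upper limit and not a likely value. The article states no safety figure to reproduce.

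**Step 2. Size of the dilution.** If the never-dosed have no recorded events, then

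rate on all randomised = rate among dosed × (29 − *k*)/29.

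With the same *k* in both arms, the difference shrinks by the same factor.

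| *k* per arm | Share never dosed | mXFP rate | Placebo rate | Difference |
|---|---|---|---|---|
| 0 | 0% | 30.0% | 10.0% | 20.0 points |
| 1 | 3.4% | 29.0% | 9.7% | 19.3 points |
| 2 | 6.9% | 27.9% | 9.3% | 18.6 points |
| 3 | 10.3% | 26.9% | 9.0% | 17.9 points |
| 5 (extreme) | 17.2% | 24.8% | 8.3% | 16.6 points |

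**Step 3. Unequal numbers.** If only the mXFP arm has never-dosed people, the difference is 30 × (29 − *k*)/29 − 10, which gives 19.0, 16.9 and 14.8 points for *k* = 1, 3 and 5. If only the placebo arm has them, it moves the other way: 30 − 10 × 26/29 = 21.0 points for *k* = 3. Under blinding there is no reason before the first dose to expect one arm to lose more than the other, so the equal case is the natural reference.

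**Step 4. If the never-dosed do have background events.** Suppose they have the placebo rate of 10%, with *k* = 3 per arm. The mXFP rate is (26 × 30% + 3 × 10%)/29 = 27.9% and the placebo rate stays at 10%. The difference is again 17.9 points. The rates no longer shrink in proportion, but the excess does.

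**Step 5. Effect on a between-arm test.** With 30% against 10% and *k* = 3 per arm, power is 0.436 on the dosed and 0.427 on all randomised. The loss is negligible; the issue is the reported percentages.

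**The case against.** The strongest reply is that this is a condensed article and that a safety population is commonly left to a full analysis plan. The adverse event sentences form their own paragraph and name no denominator, so the use of all 58 is inferred from a general sentence. The missing definition alone would indeed be no finding. What remains is the word *all*: the published rule assigns a population to every analysis, and an analysis plan with a treated-only safety set would contradict it.

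Four stronger readings are tempting, and the article does not support them.
- **Never-starters are to be expected.** A reader of the baseline visit text alone might infer this. Table 1 places the safety bloods at screening, and under that schedule the results could be known before randomisation. The two places need reconciling. Until then, never-starters are possible, with the stool condition and free withdrawal as remaining routes.
- **The dilution could be 20% or more.** Nothing supports that. It would exceed the whole implied dropout allowance of 17.2%.
- **Participants given the wrong product would distort the rates.** The Randomisation and blinding section has an independent staff member prepare the granules according to the allocation sequence, and nothing suggests errors are anticipated.
- **A planned between-arm safety test is diluted.** The chi-square sentence speaks of differences within each group, so a between-arm test is not clearly specified. That wording is a separate fault; the point about the percentages does not depend on it.

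It is also fair to say that proportional shrinkage rests on the never-dosed having no recorded events. Table 1 starts adverse event assessment at week 6, so an early leaver may have none recorded, but the article does not say how such a person would be counted.

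**Conclusion.** The point holds, as a minor one. The rule as written takes in the adverse event percentages and keeps any never-dosed participant in the harms denominator, which pulls the rates towards zero and, when the arms are similarly affected, any between-arm excess too.

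On the assumption of 1 to 3 never-dosed per arm of 29 with no recorded events, the relative loss is 3.4% to 10.3%, and an assumed 20-point excess is reported as 19.3 to 17.9 points. Five per arm (16.6 points) is the extreme. If nobody goes undosed, there is no effect. The event rates are illustrative and the never-dosed counts are assumed; the article gives neither. The efficacy analysis and the sample size are not affected.

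**What to change.** - Limit the opening sentence to *All efficacy analyses*.
- Add that adverse events and laboratory safety are summarised, and compared between arms, in participants who took at least one dose of granules, grouped by the product received.
- Report per arm the number randomised but never dosed.

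The cost is a sentence or two and a first-dose flag, which the daily compliance record described in Trial procedures and follow-up should supply. Design, sample size and primary analysis stay as they are. The downside is a slightly smaller safety denominator and slightly less favourable adverse event rates. The change should be made before unblinding.

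### Repeated-measures ANCOVA for the secondary outcomes sits badly with the intention-to-treat promise; the mixed model the plan already lists should replace it and preferably also carry the primary week-12 test

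*Protocol article*

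**What the plan says.** All the relevant statements are in the protocol article; the first four are under Statistical analysis plan.

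- General principle: "All analyses will be conducted according to the intention-to-treat principle".
- Primary analysis: ANCOVA of UAS7 between the two groups, naming baseline and weeks 6, 12 and 16.
- Directly after that: "Supplementary analyses will include a complete-case analysis and a linear mixed model analysis of all available data".
- Secondary outcomes: "Repeated measures ANCOVA will be used to test for group differences in the secondary outcomes, with adjustment for relevant baseline covariates". The software is SPSS 23.0.
- The Outcomes section puts UCT, VAS, CU-Q2oL and AAS at weeks 6, 12 and 16. It makes the UAS7 change at week 12 primary and the UAS7 changes at weeks 6 and 16 secondary. IgE and gut microbiota have one post-baseline measurement, at week 12.
- The sponsor expects some loss (Sample size): "To account for potential dropouts, a total of 58 subjects will be needed". No dropout rate is given.

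**The concern.** Classical repeated-measures ANCOVA needs a complete row for each participant. It has no means of its own to use someone seen at weeks 6 and 12 but not at week 16; that person leaves the analysis, including the two visits that were recorded. If nothing is filled in beforehand, the set analysed is the participants with full attendance, not everyone randomised. That conflicts with the intention-to-treat statement, which covers all analyses.

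Two things are at stake for the secondary outcomes. Precision is lost because collected data are discarded. The comparison is also restricted to full attenders, who may differ between arms if attendance is related to symptom control. The plan does list a model that avoids both problems, but as supplementary, in the sentence that follows the primary UAS7 analysis. It is not expressly tied to the secondary outcomes.

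**Working it through.** **1. The plan's own figure.** Inputs from Sample size: difference 10, SD 12, 80% power, two-sided 0.05. The two-sample t-test gives 23.6, rounded up to 24 per group, which matches the article (the normal approximation gives 23). Two groups need 48. The total of 58 implies a loss allowance of 1 − 48/58 = 17.2%, about 10 participants. Power with 24 per group is 80.7%.

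**2. What listwise deletion would leave.** The article gives no per-visit loss, so q = 5%, 10% and 15% are assumptions, with visits missed independently and baseline complete.

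- Participants with all three follow-up visits: 58 × (1 − q)³.
- Participants with a value at one given visit: 58 × (1 − q).
- Share of collected follow-up values thrown away: 1 − (1 − q)².
- Standard error relative to using everyone seen at that visit: √[(1 − q)/(1 − q)³] = 1/(1 − q).

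| q | Seen at a given visit | Seen at all three | Values discarded | SE ratio |
|---|---|---|---|---|
| 5% | 55.1 | 49.7 | 9.8% | 1.05 |
| 10% | 52.2 | 42.3 | 19.0% | 1.11 |
| 15% | 49.3 | 35.6 | 27.8% | 1.18 |

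So about 50, 42 or 36 of 58 are kept. The last two are below the 48 evaluable participants the design was built on.

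**3. How much depends on independence.** If the same people miss every visit, 58 × (1 − q) are kept: 55.1, 52.2 or 49.3. If each absence falls on a different person, 58 × (1 − 3q) are kept: 49.3, 40.6 or 31.9. Independence lies between. If loss were purely permanent dropout reaching 17.2% by week 16, listwise deletion would keep 58 × 48/58 = 48.

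**4. The primary outcome.** Even with nothing filled in, an ANCOVA of week-12 UAS7 needs only baseline and week 12, so the middle column above applies, not the listwise one. At 17.2% loss it keeps 48 and power is 80.7%. Power slips under 80% only at around 20% loss (79.3%).

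**5. Size of a possible bias in the primary.** A simulation with 400,000 per arm assumed SD 12, a true week-12 difference of 10, and correlations of 0.5 with baseline and 0.7 between weeks 6 and 12. Half of the worst third at week 6 leave.

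- Full 10-point effect already present at week 6 (losses about 24% placebo, 10% mXFP): week-12 ANCOVA in those observed gives 9.4; using the week-6 data as well gives 10.0.
- Effect of 5 at week 6 (losses about 20% and 13%): week-12 ANCOVA gives 9.7.
- No effect at week 6: about 10.0, so no bias.

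The standard error with 24 per group is about 12 × √(1 − 0.5²) × √(2/24) = 3.0. The largest shift, 0.6, is about 0.2 standard errors and toward the null.

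**The case against.** The strongest reply is that the article never says incomplete participants are removed. It commits every analysis to intention-to-treat. Values may be filled in before either ANCOVA by a rule set out in the full protocol or analysis plan, neither of which is shown, and an article's silence on that rule is not a fault. ANCOVA as primary with a mixed model and a complete-case analysis in support is a conventional arrangement, and the mixed-model result would be reported in any case.

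Most of this stands for the primary outcome. A reader might infer that the primary ANCOVA is itself a complete-case analysis, or that it discards everyone with any missed visit. The documents do not support either reading. A complete-case analysis listed separately as supplementary would be redundant if the primary already were one. A week-12 ANCOVA would in any event lose only those without a week-12 or baseline value.

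The reply is weaker for the secondary outcomes. There the article makes a positive choice of method, and that method can meet the intention-to-treat promise only with the help of a fill-in step. A method that uses incomplete participants directly is already in the plan.

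**Conclusion.** The point holds for the secondary outcomes measured at weeks 6, 12 and 16, on the condition that values are not filled in first. In that case repeated-measures ANCOVA would keep roughly 50, 42 or 36 of 58 at an assumed 5%, 10% or 15% independent loss per visit, and the intention-to-treat statement would not be met. The loss rates and the independence are assumptions, and the range in step 3 shows how far they matter.

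For the primary outcome this is a recommendation, not an error. No stated power or sample-size figure is wrong, and the allowance to 58 already covers about 17% loss at 80% power. The possible bias runs from none to about 0.6 UAS7 points, depending on assumed dropout and on how much of the effect is present at week 6. The reason to prefer the mixed model is that its result does not depend on a fill-in rule, and that a single week-12 contrast matches the single-time-point endpoint in the Outcomes section.

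**What to change.** 1. For UCT, VAS, CU-Q2oL and AAS, and for UAS7 at weeks 6 and 16, replace repeated-measures ANCOVA with the linear mixed model already listed. Use arm, visit, arm × visit and the baseline value as fixed effects, an unstructured covariance across visits, and all randomised participants with any post-baseline value. IgE and microbiota, with one follow-up measurement each, are not affected.
2. Preferably make the same model the primary analysis of UAS7, with the week-12 arm contrast as the single primary test, and keep ANCOVA as supplementary.
3. Keep one sensitivity analysis that departs from missing at random, since the mixed model relies on that assumption.

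The cost is a few sentences of analysis wording. No visit, measurement, sample size or software changes, because the plan already intends to fit a linear mixed model in SPSS 23.0. The real downside is the missing-at-random assumption, which item 3 addresses.
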